**Figure 1 F1:**
[figure not shown]
The study flow chart.

## Outcomes

4

### Primary outcome measure

4.1

The primary outcome measure assessed at T0, T1, T2, T3, and T4 refers to medication understanding and use self-efficacy (MUSE).^[48]^ The study will observe the stage of medication usage behavior changes for each stroke preventative medication. MUSE with a scoring scale from 0 until 32 will be used to efficiently measure confidence in the understanding of individual's perceived ability using and adhering to the prescribed medicines, which differs from other medication-specific self-efficacy measures. Both the scales; learning and taking medication, have good internal consistency (Cronbach's alpha of 0.77 and 0.68) with acceptable construct validity and predictive validity. This scale has also been validated in the Malay language version.^[49]^

Knowledge and belief of the disease, as well as its preventative medication, have been associated with medication understanding and use self-efficacy. Therefore, the primary measures assessed at T0, T2, and T4 will also consist of validated Stroke knowledge test (SKT)^[50–52]^ and Brief illness perception questionnaire (BIPQ),^[53–55]^ whereby both have acceptable validity and reliability properties and available in the Malay language version. On top of that, this study will only adapt the BMQ specific Likert scale of the belief about medicine questionnaire^[56]^ so as to hinder redundancy and patient loading. This scale will be translated and validated in Malay language in a separate study. The SKT contains 20 questions with a scoring range of 0 to 20 regarding general information on stroke, such as pathophysiology, signs and symptoms, risk factors, and treatment methods and BIPQ, on the other hand uses a 0 to 10 scoring range of Likert-type scales for the general perception of one's illness. SKT measures differences in knowledge retention between groups whereby higher scores indicate better knowledge retention. BIPQ high scores reflect vulnerable thoughts of threatened attitudes about their disease, which will correlate to the impact of the intervention. Meanwhile, the BMQ specific is comprised of 2 scales; belief about the need of preventative medication (Necessity scale), and concerns about the potential adverse effect of the medication (Concerns scale). Higher scores indicate stronger beliefs about medicine usage.

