**Results::**

The primary analysis outcomes will reflect the variances in medication understanding and use self-efficacy scores, as well as the associated factors, such as retention of knowledge, belief and perception changes, whereas stroke risk factor control, for example, self-monitoring and quality of life, will be the secondary outcomes.

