### Study design and aim

2.1

This is a single-blind, randomized controlled, parallel group, longitudinal, and exploratory trial in which patients with risk of recurrent stroke will receive either a video narrative and standard care or standard care alone. This study is due to start in the month of May 2018. The study outcomes are assessed as follows; at baseline: T0, 3 months: T1, 6 months: T2, 9 months: T3, and 12 months: T4, as outpatient follow-up. The design and the conduct of the study conform to the revised Consolidated Standards of Reporting (CONSORT) guidelines^[38]^ and adheres to Standard Protocol Items: Recommendations for Interventional Trials (SPIRIT)^[39]^ Approvals have been granted from the Malaysian Medical Research and Ethics Committee—MREC (NMRR ID-15-851-24737) and the Monash University Human Research Ethics Committee—MUHREC (ID 9640), while the study is registered with the Australian New Zealand Clinical Trials Registry—ANZCTR (ACTRN12618000174280) with Universal Trial Number (UTN) U1111-1201-3955. The research ethics committee and trial registry are notified if there are updates or protocol amendments. The study will be administered at the Neurology Department of Hospital Kuala Lumpur (HKL) in partnership with Jeffrey Cheah School of Medicine and Health Sciences, Monash University Malaysia.

The primary aim of the study is to determine if integrating a video narrative of a doctor and a patient into the standard patient education and counseling procedure will improve medication understanding and use self-efficacy, in comparison to the current standard patient education and counseling procedure. Here, the impact of reinforcement (e.g., repetition after 3 months’ interval at T1 and T2) will also be determined. Next, the secondary aim of this study is to explore the relationship between medication self-management and stroke risk factor control, as well as its effect on the quality of life among the stroke patients. The study achieves an endpoint if stroke recurs.

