### Sample size

2.3

A power analysis was carried out for an independent *t* test using the G∗Power version 3 to determine a sufficient sample size using an alpha of 0.05 and a power of 0.80.^[40]^ The estimation involved a medium effect size (*w* = 0.4) based on an average of effect sizes from similar recent studies associated to patient education in stroke, IMB, HBM, video narrative, and self-efficacy.^[25,41–43]^ However, sample size calculation according to stratification of stroke risk factors is not feasible because this is a disease with various underlying comorbidities and treatment heterogeneity. Thus, the desired sample size is 200 (100 each in intervention and control groups) are needed. With an estimated 15% attrition rate, 115 in each group will be recruited, thus yielding a target total sample size of 230.

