### Statistical analysis

4.3

Data entry will be done independently by a clinic staff nurse and verified by another. Hardcopies of data collection forms and outcome measures will be kept in a locked safe, whereas softcopies are to be deposited at the repository center (Lab Archives), both at Monash University in Malaysia. Only the principal investigators ([name]), ([name]), and ([name]) have access to the interim results and makes the final decision to terminate the trial. The study team ensures that patients’ identity and personal information are coded to maintain confidentiality. In addition, ([name]) and the biostatistician ([name]), who will also be blinded, will conduct the statistical analysis by using International Business Machines Statistical Package for the Social Sciences (IBM SPSS; IBM Corp. Released 2013. IBM SPSS Statistics for Windows, Version 22.0. Armonk, NY) (v.22). The initial analysis will consist of descriptive statistics on demographic data, such as frequency distributions. Meanwhile the mean differences in primary and secondary outcomes are compared by using *t* tests or equivalent statistical method, whereas categorical outcomes are matched using chi square test. *P* values <.05 are considered statistically significant. Generalized mixed model analysis is adapted to investigate the variances between groups over time for all outcomes evaluated at the allocated time. Furthermore, the association between medication understanding and use self-efficacy, stroke knowledge, illness perception scores, as well as engagement in self-monitoring and clinic appointment attendance will be tested, as they seem to be critical indicators of behavioral changes. Multivariable analysis will be employed to examine the influence of the video narratives on stroke risk factor control and their covariates.^[61]^ Multiple imputation will be adapted to handle missing data if it occurs. In addition, withdrawn patients’ feedback about the intervention will be analyzed.

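### The primary aim and sample size concern MUSE alone, but section 4.1 and the abstract make further scales primary, with an unadjusted P<.05

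*Protocol article*

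**What the plan says.** **One outcome.** Section 2.1 (Study design and aim) asks whether adding the video narrative "will improve medication understanding and use self-efficacy, in comparison to the current standard patient education and counseling procedure". No other scale appears in the primary aim. Section 2.3 (Sample size) is for a single independent t test, "using an alpha of 0.05 and a power of 0.80", and concludes that "the desired sample size is 200 (100 each in intervention and control groups) are needed". Section 4.1 opens in the singular, with MUSE as the primary outcome measure, assessed at T0 to T4.

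**Several outcomes.** Section 4.1 goes on: "Therefore, the primary measures assessed at T0, T2, and T4 will also consist of validated Stroke knowledge test (SKT", and BIPQ is named in the same sentence. The BMQ, with its Necessity and Concerns scales, is added next under the same heading. It is not itself labelled primary and is given no visits of its own. The abstract takes the wider view too: "The primary analysis outcomes will reflect the variances in medication understanding and use self-efficacy scores, as well as the associated factors", with knowledge, belief and perception as its examples. Section 4.2 lists the secondary outcomes separately, and none of these scales is among them.

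**Analysis.** Section 4.3 compares mean differences in primary and secondary outcomes by t tests or an equivalent method, without naming the visit. It states that P "values <.05 are considered statistically significant". It also plans a generalized mixed model of group differences over time for all outcomes. It describes no adjustment or ordering of the primary scales. Section 2.1 calls the trial exploratory.

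**The concern.** A design with 5% error and 80% power for one test is joined to a primary set of four instruments (five scales if the BMQ scales count separately), most of them outside the stated aim. A reader of the results could not tell which comparison answers the primary question. If MUSE showed no difference and stroke knowledge did, section 4.1 and the abstract would allow the knowledge result to be presented as a primary finding. Section 2.1 and the sample size would not. The 5% error rate implied by the sample size holds only if there is one primary test.

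**Working it through.** **1. The plan's own figure.** Inputs from 2.3: alpha 0.05, power 0.80, effect size 0.4. The document labels the effect size w; here it is read as a standardised mean difference, which is what a t test needs. Two-sided testing is assumed because the document does not state it.

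n per group = 2 × (1.960 + 0.842)² / 0.4² = 2 × 7.85 / 0.16 = 98.1, so 99. The exact t calculation gives 99.08, so 100 per group and 200 in total. Power at 100 per group is 0.804. A one-sided test would need 78. The stated figure is therefore reproduced as one two-sided test with no allowance for further primary tests.

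**2. Count of primary comparisons.** MUSE is taken as one total score (0 to 32) with four post-baseline visits, T1 to T4. SKT and BIPQ have two each, T2 and T4. The BMQ is assumed to share T2 and T4.

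- One test per scale: 4 (BMQ as one score) or 5 (two BMQ scales).
- A test at every post-baseline visit: 4 + 2 + 2 + 2 = 10, or 4 + 2 + 2 + 4 = 12.

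**3. Chance of at least one P<.05 when the video has no effect on any scale.** For k independent tests this is 1 − 0.95^k:

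- k = 4: 1 − 0.8145 = 18.5%
- k = 5: 1 − 0.7738 = 22.6%
- k = 10: 1 − 0.5987 = 40.1%
- k = 12: 1 − 0.5404 = 46.0%

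For correlated tests, 200,000 sets of normal test statistics were simulated, counting any |z| > 1.96. The correlation between two statistics was the between-scale value (1 within a scale) times the between-visit value (1 at the same visit). The documents give no correlations, so these are assumptions.

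| Reading | Independent | Correlated |
|---|---|---|
| One test per scale, 4 scales | 18.5% | 15.5% (r = 0.5), 13.1% (r = 0.7) |
| One test per scale, 5 scales | 22.6% | 18.2% (r = 0.5), 14.8% (r = 0.7) |
| Every visit, 10 tests | 40.1% | 35.8% (scale 0.2, visit 0.5) to 28.3% (scale 0.5, visit 0.7) |
| Every visit, 12 tests | 46.0% | 41.2% (scale 0.2, visit 0.5) to 32.1% (scale 0.5, visit 0.7) |
| MUSE alone at four visits | 18.5% | 15.6% (visit 0.5), 13.1% (visit 0.7) |
| MUSE alone, one test | 5% | 5% |

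With both correlations at 0.7, the per-visit figures fall to 24.4% (10 tests) and 26.8% (12 tests), still far above 5%.

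**4. Keeping all scales primary with a Bonferroni correction.** For four tests alpha is 0.05/4 = 0.0125: power at 100 per group falls to about 63%, and about 141 per group would be needed for 80%. For five tests alpha is 0.05/5 = 0.01: power is about 60%, and about 148 per group would be needed.

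**The case against.** **The per-visit figure assumes an analysis that the plan does not fix.** A reader might infer that 4.3 tests all 12 comparisons at .05, so that the false-positive rate simply is 30-45%. The document does not support that. It names no visit for the t tests, and it plans a mixed model that could give one test per scale, for which the range is 13-23%. This objection stands, so both ranges are given.

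**No success rule is written.** A reader might also infer that any significant scale at any visit counts as success. Section 4.3 says only when a P value is called significant. The figures are therefore conditional on results being reported that way.

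**The primary aim itself may be safe.** Extra scales do not inflate the error for a question about MUSE alone. One MUSE test keeps 5%, and four per-visit MUSE tests give 13-19%. So it would be too strong to say that the trial cannot answer its primary aim at the 5% level.

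**The trial is exploratory, and an analysis plan may exist.** The label weakens a strictly confirmatory reading. The primary visit and the multiplicity method are commonly left to an analysis plan, so their absence is not held against this article. Nor is the separate validation of the Malay BMQ. Neither point, however, reconciles a one-outcome aim and sample size with the several-outcome list in 4.1 and the abstract.

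**The BMQ is primary only by placement.** This is true, and the abstract's mention of belief supports it only indirectly. Without the BMQ, three instruments remain, and 4.1 expressly calls SKT and BIPQ primary measures.

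**Conclusion.** The concern holds as a conflict within the document: sections 2.1 and 2.3 rest on one primary outcome, while 4.1 and the abstract list several, and 4.3 applies an unadjusted threshold. If a significant result on any primary scale were reported as a primary effect, the chance of at least one false positive would be about 13-23% with one test per scale (4 or 5 scales, correlation 0 to 0.7). It would be about 28-46% with a t test of every scale at every post-baseline visit (10 or 12 tests; from between-scale 0.5 with between-visit 0.7, up to independence). These sizes rest on assumed correlations, two-sided tests and BMQ visits at T2 and T4. Every multi-scale reading is more than twice the nominal 5%. Given the exploratory label and the absence of a stated success rule, this is a point that should be fixed rather than one that undermines the trial.

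**What to change.** Make the MUSE total score the only primary outcome, as the primary aim already does. Name in advance one two-sided 5% test of it: either the group difference at one stated visit, or one stated contrast from the mixed model already planned in 4.3. Both control the error equally well. The choice should take account of the reinforcement question that 2.1 places under the primary aim.

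Move SKT, BIPQ, both BMQ scales and the remaining MUSE comparisons to secondary outcomes, reported with confidence intervals and no claim of a primary effect. Align 4.1, 4.3 and the abstract, and check that the trial registration, which was not available here, agrees.

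The cost is wording only; the planned sample of 100 per group still fits a single test. The downside is that no primary claim can then be made on knowledge, illness perception or medication beliefs. If the sponsor wants to keep those claims, the alternative is an adjusted threshold, with the loss of power or the larger sample shown in step 4 of the working.

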### Secondary outcome measures

4.2

Secondary main outcome measures include patient's stroke risk factor control which could be either on smoking habit, blood pressure, blood glucose, cholesterol, triglycerides, or international normalized ratio (INR) assessed at T0, T1, T2, T3, and T4. This outcome translates adherence to treatment and lifestyle behavioral changes such as diet and stress control, whereas assessment at T2 and T4 includes health-related quality of life, clinic appointment attendance report, and self-monitoring report.

Based on past findings, most of stroke patients were diagnosed with hypertension as their primary stroke risk factor.^[36,37]^ It is defined that blood pressure (BP) control as at or below 140/90 mmHg for patients with no diabetes and at or below 130/80 mmHg for patients with diabetes.^[45,46]^ Therefore, differences of BP will be measured at every session by using calibrated blood pressure device at the neurology clinic. Whereas, the gathered blood samples, are sent and assessed at the hospital laboratory department. The risk of recurrent stroke would be at double-fold if the patient is diagnosed with both hypertension and diabetes. Diabetes control is defined as at A1c level <6%, venous fasting plasma level <7.0 mmol/L, and random plasma level <10 mmol/L. In addition, the stroke symptoms would worsen for patients with underlying cardiovascular disease (CVD). Hence, those with hyperlipidemia control is defined as LDL-C <3.4 to 4.2 mmol/L and triglycerides <8.3 mmol/L.^[45,57,58]^ Furthermore, INR control for stroke patients with atrial fibrillation is 2.0 to 3.0.^[59]^

The overall secondary outcome measures reflect the perceived benefit to quality of life. This study will use the Short Form (36) Health Survey (SF-36) questionnaire as its quality of life outcome measure.^[60]^ The SF-36, which consist of a 36-item questionnaire, is best used in general clinical practice. The construct domains contain one's perceived physical and mental limitation, such as physical functioning, mental health, emotional problems, social life purpose, general health perceptions, and body pain. The sum of scores is between 0 (worst-perceived health state) and 100 (best-perceived health state). The measure will be able to evaluate the degree of perceived difficulty experienced between both control and intervention groups. This questionnaire has been validated in various languages with acceptable psychometric properties in many clinical settings. Besides, permission has been granted for this study to use the outcome measures from all the respective authors.

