### Study procedures

3.1

With the supervision of a research neurologist, patient screening and randomization will be carried out by a clinic staff nurse who is not involved in this research. Patients will then complete their baseline assessments at the outpatient Neurology clinic. The neurologists will be blinded after the assignment. They will be advised to not to prompt patients regarding reception of intervention. One of the researcher ([name]) who is a pharmacist and a clinical educator, will conduct the baseline assessment. Patients randomized into the intervention arm will be displayed the video immediately after their clinic visit. All patients, regardless of study arm, will receive appropriate standard stroke treatment and medication management. At each consequent visit, the researcher will assess the level of medication understanding and use self-efficacy, while evaluation of stroke risk blood parameters will be done by the staff nurse at the clinic. The researcher will send reminder calls 3 days in advance to promote retention. At each clinic visit, both groups will receive MTAC standard care reminders to encourage self-monitoring, to modify lifestyle, to follow-up clinic appointments, and to enquire regarding their medications. Patients who miss their visits, move too far away, are referred to other outpatient clinics, and those who fail to respond up to 4 times of reminders will be noted as lost to follow-up and eventually withdrawn from the study. Also, if there is a need of unblinding due to the intervention's effect, the patient's allocation will be revealed to their neurologist and that patient is withdrawn from the study. These effects will be recorded and reported in the data analysis.

At each session, the patients will meet the neurologist first for their follow-up treatment review, and next, have further check on self-monitoring practice and lifestyle changes. The clinic staff nurse will assess their blood pressure and other appropriate blood parameters. After that, the clinic staff nurse will guide the patients into a quiet room, where the researcher will meet them individually for the outcome assessment or video viewing. The patients will view the video at baseline: T0, 3rd month: T1 and 6th month: T2 immediately after outcome measure assessment (Fig. 1).

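### As written, SF-36 is scheduled at T2 and T4 with no baseline, so change from baseline cannot be estimated and the quality-of-life comparison cannot be adjusted for starting score

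*Protocol article*

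**What the plan says.** All places are in the protocol article.

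- **Quality of life.** Secondary outcome measures gives its times as "assessment at T2 and T4 includes health-related quality of life, clinic appointment attendance report, and self-monitoring report". The instrument is fixed in the same section: "This study will use the Short Form (36) Health Survey (SF-36) questionnaire as its quality of life outcome measure".
- **Risk factors.** The same sentence sets this against the risk-factor measures, which run through "international normalized ratio (INR) assessed at T0, T1, T2, T3, and T4".
- **Other questionnaires.** Primary outcome measure puts MUSE at all five visits. The reduced questionnaire schedule keeps the baseline: "the primary measures assessed at T0, T2, and T4 will also consist of validated Stroke knowledge test (SKT" and the illness perception questionnaire.
- **Video timing.** Study procedures: "The patients will view the video at baseline: T0, 3rd month: T1 and 6th month: T2 immediately after outcome measure assessment".
- **Aim.** Study design and aim includes quality of life in the secondary aim, which is to explore how self-management relates to risk-factor control, "as well as its effect on the quality of life among the stroke patients".
- **General visit list.** The same section says "The study outcomes are assessed as follows; at baseline: T0, 3 months: T1, 6 months: T2, 9 months: T3, and 12 months: T4", without tying any outcome to any visit.
- **Analysis.** Statistical analysis: "Generalized mixed model analysis is adapted to investigate the variances between groups over time for all outcomes evaluated at the allocated time". Missing data are to be handled by multiple imputation.

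**The concern.** Quality of life is grouped with clinic attendance and self-monitoring reports. Those two accrue during follow-up and need no baseline. SF-36 is a health-state score that patients already have at entry, and in stroke survivors it can be expected to vary widely. The Introduction says that about a third of acute strokes end in moderate to severe disability, and the Randomization section describes permuted blocks with no stratification factor.

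T2 cannot stand in for a baseline, because by then the intervention arm has seen the video twice. Four things are at stake:

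- an estimate of change in quality of life from entry;
- precision of the arm comparison at T2 and T4;
- a predictor for imputing missing SF-36 scores. A patient lost before T2 has no SF-36 value of any kind;
- adjustment in the exploratory analysis relating self-management to quality of life. That is an association, which randomisation does not protect. Patients in better health at entry may both manage their medicines better and score higher later.

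**Working it through.** **1. Which outcomes have a T0 in the text**

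| Outcome | Times named | T0 named? |
|---|---|---|
| MUSE | T0, T1, T2, T3, T4 | yes |
| Stroke knowledge, illness perception | T0, T2, T4 | yes |
| Beliefs about medicines (specific scale) | none of its own; the preceding sentence suggests T0, T2, T4 | by inference |
| Risk factors | T0, T1, T2, T3, T4 | yes |
| SF-36 | T2, T4 | no |
| Attendance, self-monitoring | T2, T4 | no, and not needed |

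The general five-visit list does not fill the gap. It cannot apply to every outcome, since the knowledge and illness perception questionnaires skip T1 and T3. Where a reduced schedule was meant to include baseline, T0 was written out.

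**2. The plan's own sample size**

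Inputs from Sample size: standardised difference 0.4, alpha 0.05, power 0.80, independent t test. Two-sided, the t-test calculation gives 99.08 per arm, rounded up to 100. Power at 100 per arm is 0.804. The stated 100 per arm reproduces. It was not derived for SF-36; it is used below only as a yardstick.

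**3. What a baseline score would add**

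Let r be the correlation between baseline and follow-up SF-36. The documents do not give it, so 0.3 to 0.7 is assumed. With baseline as a covariate:

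- variance factor = 1 − r²; standard-error factor = √(1 − r²)
- power ≈ Φ( 0.4 / [√(2/100) × √(1 − r²)] − 1.96 )
- difference detectable at 80% power = 0.398 × √(1 − r²), in SD units

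| r | Variance factor | Variance cut | SE factor | Power at 0.4 SD | Detectable difference |
|---|---|---|---|---|---|
| no baseline | 1.00 | – | 1.000 | 0.80 | 0.40 SD |
| 0.3 | 0.91 | 9% | 0.954 | 0.84 | 0.38 SD |
| 0.5 | 0.75 | 25% | 0.866 | 0.90 | 0.34 SD |
| 0.7 | 0.51 | 49% | 0.714 | 0.98 | 0.28 SD |

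Worked line, r = 0.5: √(2/100) = 0.1414; 0.4 / (0.1414 × 0.866) = 3.27; 3.27 − 1.96 = 1.31; Φ(1.31) ≈ 0.90.

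**4. Why adjustment and not simple change scores**

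The variance of a change score relative to a follow-up score is 2(1 − r): 1.4 at r = 0.3, 1.0 at r = 0.5, 0.6 at r = 0.7. Below r = 0.5 an analysis of raw change is less precise than follow-up alone. Adjustment for baseline is never worse in this comparison.

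**5. Size of chance imbalance**

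With 100 per arm, the baseline difference in SF-36 has standard error √(2/100) = 0.14 SD, so a 95% range of about ±0.28 SD. The chance that it exceeds 0.2 SD in either direction is 2 × [1 − Φ(0.2/0.1414)] = 0.16. As scheduled, such a difference could not be seen.

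**The case against.** **The schedule is not certain.** The text does not say that T2 and T4 are the only times, the general list mentions baseline, Study procedures refers to baseline assessments without naming them, and the flow chart is not shown. This stands as a limit. A reader might infer that SF-36 is definitely not taken at T0; the supportable statement is that the text gives it no T0.

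**The arm comparison is not invalid.** A reader might infer that chance imbalance in disability would be confounded with the video's effect and so make the T2 and T4 comparison unsound. The documents do not support that. Allocation is randomised, so the difference is unbiased in expectation, and its standard error already covers chance imbalance. The loss is in precision and interpretation.

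**The analysis section does not contradict the schedule.** It is tempting to say that the mixed model over time needs a baseline. The model is limited to each outcome's own times, and two follow-up visits permit a group-by-time model. Change from T2 to T4 can also be estimated, though both points follow the intervention. Nor does the plan promise change from baseline in quality of life: SF-36 is described as a contrast between arms.

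**The gain may be smaller.** The correlation is assumed, and at 0.3 the gain is modest. The table compares adjustment with no adjustment at all. Baseline illness perception, MUSE, risk factors and demographics are collected and could recover part of the loss; how much is unknown. The trial calls itself exploratory, and the authors weighed patient burden when choosing instruments. All of this is fair. It lowers the stakes but does not argue against one more form at a visit already held.

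**Conclusion.** The concern holds as a missed, inexpensive improvement to a secondary outcome, not as an error that invalidates the trial. On the text as it stands, SF-36 has no baseline and its first measurement follows two video viewings. The trial would then be unable to:

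- estimate change in quality of life from entry;
- examine or adjust for baseline SF-36;
- use a baseline score when imputing SF-36 or when relating self-management to it.

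For an assumed correlation of 0.3 to 0.7, the forgone cut in variance is about 9 to 49%. In power terms that is 0.80 against roughly 0.84 to 0.98, at 100 per arm and a 0.4 SD difference. These figures rest on that assumption, on the sample-size section's effect size being carried over to SF-36, and on no other covariates being used. The reading of the schedule is subject to the flow chart that is not shown.

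**What to change.** Add SF-36 to the T0 assessment and state this in Secondary outcome measures. It should be completed before the first video viewing at the latest. Completion before allocation is revealed would be better, but Study procedures places randomisation ahead of the baseline assessments, so that would mean reordering the visit.

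Analyse T2 and T4 scores with T0 SF-36 as a covariate, not as raw change, and include T0 SF-36 in the imputation model.

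If the flow chart already lists SF-36 at T0, correct the text to match. If a follow-up-only measurement is intended, say so and describe the quality-of-life analysis as a comparison at T2 and T4 without change from baseline.

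The cost is one 36-item questionnaire at an existing visit and a slightly longer baseline session for the patient. A baseline not taken before the first viewing cannot be recovered later.

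### The LDL-C control limit is an upper bound written as a range, and the diabetes rule does not say how its three measures combine, so binary control of LDL-C or glucose is not reproducible as written

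*Protocol article*

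**What the plan says.** Section 4.2 of the protocol article names stroke risk factor control among the secondary outcomes, assessed at T0 to T4, and then defines control for each factor:

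- Lipids: "those with hyperlipidemia control is defined as LDL-C <3.4 to 4.2 mmol/L and triglycerides <8.3 mmol/L".
- Diabetes: "Diabetes control is defined as at A1c level <6%, venous fasting plasma level <7.0 mmol/L, and random plasma level <10 mmol/L".
- Blood pressure: "control as at or below 140/90 mmHg for patients with no diabetes and at or below 130/80 mmHg for patients with diabetes".
- Anticoagulation: "INR control for stroke patients with atrial fibrillation is 2.0 to 3.0".

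Section 4.3 (Statistical analysis) says that "the mean differences in primary and secondary outcomes are compared by using" t tests or an equivalent method, and that "categorical outcomes are matched using chi square test". It adds a generalized mixed model for differences between groups over time, covering all outcomes. It also plans a further model: "Multivariable analysis will be employed to examine the influence of the video narratives on stroke risk factor control and their covariates". The article does not say whether risk factor control enters that model as a yes/no variable or as a measured value.

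**The concern.** A control definition has to place every patient to whom it applies in one of two classes. The LDL-C definition does not. A value of 3.8 mmol/L is controlled if the limit is 4.2 and uncontrolled if it is 3.4, and no patient group is attached to either end. The diabetes definition is unclear in a different way: it does not say what decides when only some of the three measures are available, or whether one failing measure is enough to count as uncontrolled.

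If control is analysed as yes/no for these two factors, two competent analysts could follow the article and report different proportions. If the gap were closed only once results by arm could be seen, the choice of rule could be influenced by them.

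**Working it through.** The article states no control rate, and no power for one, so there is no figure to reproduce. The check has three parts.

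**1. Can each definition be applied?**

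| Factor | Rule in section 4.2 | Assigns one class? |
|---|---|---|
| Blood pressure | One limit per diabetes status | Yes |
| Triglycerides | Single upper limit, 8.3 mmol/L | Yes |
| INR (atrial fibrillation) | Closed interval, 2.0 to 3.0 | Yes |
| LDL-C | Upper limit of 3.4 to 4.2 mmol/L | Not from 3.4 up to 4.2 |
| Diabetes | A1c, fasting and random limits, joined by *and* | Only if the combination rule is known |

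The blood pressure rule shows how two limits can be made usable: each is tied to a named patient group. The LDL-C rule lacks that tie. The INR interval is not a parallel case, because a target interval has two working ends, whereas the LDL-C rule has a less-than sign in front of a range.

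**2. How large could the undefined LDL-C band be?**

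The inputs are the two limits from section 4.2 (3.4 and 4.2 mmol/L) and an assumed normal distribution of LDL-C among patients with hyperlipidemia. The mean and SD are assumptions; the article gives neither.

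Undefined share = Φ((4.2 − mean)/SD) − Φ((3.4 − mean)/SD)

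For mean 3.0 and SD 1.0: Φ(1.2) − Φ(0.4) = 0.885 − 0.655 = 0.230.

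| Assumed mean | Assumed SD | Below 3.4 | Below 4.2 | Undefined |
|---|---|---|---|---|
| 2.5 | 0.8 | 87.0% | 98.3% | 11.4% |
| 2.5 | 1.0 | 81.6% | 95.5% | 13.9% |
| 3.0 | 0.8 | 69.1% | 93.3% | 24.2% |
| 3.0 | 1.0 | 65.5% | 88.5% | 23.0% |
| 3.5 | 0.8 | 45.0% | 80.9% | 35.9% |
| 3.5 | 1.0 | 46.0% | 75.8% | 29.8% |

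The band holds 11% to 36% of values over this grid. (The last column was computed before rounding.)

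**3. How far apart are the readings of the diabetes rule?**

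Assume that each of the three criteria is met by the same share of patients (30% or 50%), with underlying normal variables that have equal pairwise correlation of 0.5 to 0.8. These figures are also assumptions.

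| Share meeting each criterion | Correlation | All three met | At least one met |
|---|---|---|---|
| 30% | 0.5 | 10.1% | 53.0% |
| 30% | 0.7 | 14.4% | 47.3% |
| 30% | 0.8 | 17.2% | 43.9% |
| 50% | 0.5 | 25.0% | 75.0% |
| 50% | 0.7 | 31.0% | 69.0% |
| 50% | 0.8 | 34.6% | 65.4% |

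The two columns are the strictest and loosest ways to combine the criteria: 10% to 35% controlled against 44% to 75%. A rule based on whichever single measure was taken would give the assumed 30% or 50%, which lies between them.

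**The case against.** **Much of the planned analysis does not use the limits.** Section 4.3 compares mean differences and adds a mixed model over time, and both can be run on measured LDL-C, glucose and A1c. It does not say that the chi-square test will be applied to LDL-C or glucose control; smoking habit is also listed in section 4.2 and is naturally categorical. This stands. It limits the point to whatever binary control analyses are carried out.

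**The article is condensed, and a full protocol or SAP may settle the rule.** That would excuse a missing detail. It does not excuse the LDL-C limit, which is stated here in a form that cannot be applied. The objection has more force for the combination of glucose measures, which is a usual SAP detail.

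**The diabetes sentence can be read sensibly.** It may be a list with one limit per measure. Even a strict *and* classifies a patient who has all three values: one failure means not controlled. A reader might infer that no visit could ever satisfy the rule because a sample is either fasting or random. The article does not support that, since it refers to samples in the plural and gives no sampling schedule. What stands is an ambiguity.

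**Nobody says the limit will be picked after the data are seen.** A reader might infer this, but nothing in sections 4.2 or 4.3 says so. The biostatistician is to be blinded, and whichever limit is used would apply to both arms. So only the opportunity for a later choice can be claimed, and no bias in the between-arm difference has been shown.

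**Conclusion.** The point holds for two definitions. The LDL-C limit is a stated rule that leaves patients with hyperlipidemia and values from 3.4 up to 4.2 mmol/L unclassified. The diabetes rule is ambiguous about how its measures combine. Binary control analyses of either are not reproducible from the article.

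The 11% to 36% for LDL-C rests wholly on the assumed distributions and applies only to patients with hyperlipidemia. It measures how many values are undecided, and is not an error in a treatment effect. The diabetes figures are likewise illustrative.

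It would go too far to say that the risk factor control definitions in general cannot classify patients: the blood pressure, triglyceride and INR rules can be applied as written. The primary outcome, MUSE, does not depend on these limits, and the trial describes itself as exploratory. This is an inexpensive correction to secondary outcomes.

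**What to change.** Before unblinding:

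1. Reconcile the LDL-C wording in section 4.2 so that each defined patient group has exactly one limit. Which value belongs to which group is a clinical decision for the investigators, and none is proposed here.
2. State in section 4.2 how A1c, fasting glucose and random glucose combine, and what decides when only some are available or when they disagree.
3. State in section 4.3 that the main between-arm comparison of LDL-C, triglycerides, A1c and blood pressure uses the measured values, adjusted for the T0 value, with proportion controlled as supportive. The article already names a comparison of means; the additions are the T0 adjustment, which the stated t test lacks, and the order of priority.

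The cost is a few sentences in sections 4.2 and 4.3. It needs no new data and no change to the sample size. If the SAP already contains these rules, only the published wording needs to be brought into line.
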